## 4. Ethics and dissemination

The study is conducted in accordance with the standards of Good Clinical Practice and in agreement with the Declaration of Helsinki. Written informed consent will be provided by the research team. The information letter includes written information about the study, the purpose and procedures, the voluntary nature of participation, and the option to withdraw at any time. If needed, clinicians will help to clarify the written information. The participants are guaranteed confidentiality and that their data are stored on a secured server except the brain imaging data, which will be made anonymously public. It is impossible to identify the participants from the brain imaging data, and at the same time, open science is supported by publishing the data. The participants will be informed about the public data sharing on a group level without any personal information in their information letter and asked for their consent for it. In addition, the participants in the study were invited to an information meeting before the start of the study, where verbal explanations of all the procedures were given. Any adverse events or harm arising from study participation will be reported and managed by the instructors and the research team in accordance with ordinary healthcare routines.

Data are collected in both pen-and-paper and digital formats and securely stored at the University Health Care Research Center. The questionnaires and tests will be pretested on a conditions-appropriate group during the pilot study to determine whether the wording and length of the questionnaire and tests were appropriate for the study’s target group. The pilot study investigated different aspects of intervention fidelity. No unauthorized persons have access to the collected data, during the study, apart from the brain imaging data as mentioned above. All the data collected are coded to protect the study participants’ identification. All data and the code list are stored securely and separately to prevent unauthorized persons from having access to them.

## 5. Adverse event and safety monitoring

Instructors in the study will regularly ask participants in the intervention how they felt after the previous session. Any adverse events related to the participation in intervention will be recorded and assessed in terms of severity which will be reported to the principal investigator, serious adverse events will be recorded in the patient’s medical chart.

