The main study will be a prospective randomized controlled trial (RCT) with 2 parallel groups: an intervention group (30 participants) and a control group (30 participants) of adults with schizophrenia or disorders with symptoms similar to schizophrenia, as described in section “2.3.1. Inclusion criteria.” The intervention consists of sessions on mixed exercise program with creative movement two times a week for 12 weeks in addition to standard medical care as described in section “2.9 Standard care.” Each group will include 4–6 participants under the guidance of two instructors. The control group receives standard medical care and gets access to the video-links after the 12-month follow-up. Most outcomes are measured at baseline, after 6 and 12 weeks, 6 and 12 months (see Figure 1 for details). At all follow-ups, data is collected for both the intervention and control groups. The timeframe of the main study is from autumn 2023 to spring 2025. The study adheres to the standard methodology of intervention research. This protocol is conducted according to the SPIRIT (Standard Protocol Items: Recommendations for Interventional Trials) guidelines (Chan et al., 2013). The study will be reported according to the CONSORT (Consolidated Standards of Reporting Trials) guidelines (Schulz et al., 2010), and COREQ (Consolidated Criteria for Reporting Qualitative Research; Tong et al., 2007).

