### 2.15. Adherence

Intervention adherence will be noted by the instructors during both pilot study and main study. To stimulate high adherence to the intervention throughout all the intervention time period, we will work in close collaboration with the clinic, both for reminding about the importance of intervention participation during the 12 weeks and in practical issues regarding getting to the studio in time. To keep the creative physical exercise sessions motivating and interesting, the focus will be on enjoyment, social inclusion and increasing body movement in harmony with music. In addition, the fact that the intervention consists of three different parts with separate themes will hopefully stimulate adherence motivation. To retain as many participants as possible, reminder text-messages and emails will be sent to participants. Notes about participants who discontinue or deviate from the study will be made.

Randomization will minimize bias, but we will assess any change in the treatment plan of the participants including medication, if they stop taking their medication and become ill, or if they change to a better medication and improve because of the intervention.

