#### 3.2.2. Quality of life, social performance, and depressive symptoms

Patients will fill in quality-of-life questionnaires (EQ-5D-5L) before, after the intervention and at follow ups. The patients’ psychiatrist and a person who knows the patients, such as a family member, will evaluate the state of the patient before and after the intervention, and then, the family member will also be asked about their experience on burden of care. The Personal Social Performance scale (PSP, internal consistency reliability for the four items exceeding 0.70 for people with schizophrenia, Kawata and Revicki, 2008) assesses socially useful activities, personal and social relationships, self-care and disturbing and aggressive behaviors. The Calgary Depression Scale for Schizophrenia (CDSS, high inter-rater reliability with an intraclass correlation of 0.895 and Cronbach’s alpha 0.79 for people with schizophrenia, Addington et al., 1993) is a nine-item clinician rated outcome measure that assesses the level of depression in people with schizophrenia.

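### Adverse events are actively sought only in the intervention arm and recorded only if related to the intervention, so adverse event rates cannot be compared between arms, even descriptively

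*Protocol article*

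**What the plan says.** Section 5 (Adverse event and safety monitoring) fixes three things.

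- Who is asked, by whom and about what: "Instructors in the study will regularly ask participants in the intervention how they felt after the previous session".
- What is recorded: "Any adverse events related to the participation in intervention will be recorded and assessed in terms of severity". These events are reported to the principal investigator.
- Serious events: "serious adverse events will be recorded in the patient’s medical chart".

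Section 4 (Ethics and dissemination) has a second statement with a different scope: "Any adverse events or harm arising from study participation will be reported and managed by the instructors and the research team".

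Other sections bear on harm without using the term. Section 2.2 says of outcome data: "At all follow-ups, data is collected for both the intervention and control groups". Section 2.15 says: "we will assess any change in the treatment plan of the participants including medication, if they stop taking their medication and become ill", with no arm restriction. Table 2 schedules PANSS, CGI, CDSS, PSP, EQ-5D-5L and physical measures at baseline, weeks 5 to 7, week 12, and months 6 and 12. Its rows include no adverse event item.

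**The concern.** Section 5 states a rule that separates the arms; it does not merely leave detail to a fuller document. Enquiry is tied to sessions, which only one arm attends, and recording is tied to relatedness to an intervention that only one arm receives. Whatever is counted in the intervention arm therefore has no counterpart among controls.

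This matters because the trial tests a new programme with moderate-to-vigorous exercise and emotional expression in symptomatic patients, and section 2.15 itself foresees that some may become ill. If relapses, admissions or injuries occur in the intervention arm, the reader will want to know how often they occurred under standard care alone. The adverse event process as written cannot answer that, although both arms attend the same assessment visits.

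**Working it through.** The protocol states no adverse event rate, safety sample size or safety power, so there is no figure to reproduce. The check is of the text, with a short illustration.

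**1. The routes side by side**

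| Route | Who can enter it | Filter by cause | Enquiry among controls |
|---|---|---|---|
| Section 5, instructor question | Intervention patients at sessions | Question concerns the previous session | None |
| Section 5, recording rule | Intervention patients only, since the event must relate to the intervention | Yes | None |
| Section 5, serious events | No arm limit stated | None stated | None described; goes to the medical chart, no trial record named |
| Section 4 | Possibly both arms, e.g. harm from study testing | Yes, must arise from study participation | None described |
| Section 2.15, treatment change and illness | No arm limit stated | None stated | Assessment stated, method not given |
| Table 2 scales and physical measures | Both arms | None | Yes, but scores rather than events |

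No row gives an all-cause event count collected in the same way in both arms. The chart clause comes closest. It describes no extraction into trial data, however, and section 2.9 sets the minimum for routine outpatient contact at one visit a year.

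**2. Number of enquiries**

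There are 24 sessions. The question concerns the previous session, so it cannot be asked at session 1: 24 − 1 = 23 at most. The text says only that it is asked regularly, so 23 is a ceiling. Controls have 0 sessions and so 0 enquiries by this route.

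**3. What the observed difference would estimate**

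Let r_I and r_C be the true all-cause event probabilities, and s the share of intervention-arm events that pass the section 5 rule. Controls pass with share 0.

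- Observed difference = r_I·s − r_C·0 = r_I·s.
- Observed minus true difference = r_I·s − (r_I − r_C) = r_C − r_I(1 − s).

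Control experience (r_C) does not enter the observed quantity at all. The direction of the error also depends on unknowns. With assumed rates r_I = 30% and r_C = 10%, the error is 0.10 − 0.30(1 − s). This is zero at s = 2/3, positive above it and negative below it. It cannot be said in advance that the count would be biased against the intervention.

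**4. What equal collection could deliver**

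- Zero events in n patients leaves a one-sided 95% upper bound of 1 − 0.05^(1/n). For n = 30 this is 9.5%. For n = 22 (30 less 25% dropout is 22.5, rounded down) it is 12.7%.
- Power at two-sided 0.05 with 30 per arm, under assumed rates: about 49% for 10% against 30%, and 78% for 10% against 40%.

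Even with identical ascertainment the comparison would be descriptive.

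**The case against.** The strongest reply is that controls are far from unobserved. PANSS, CGI, CDSS and PSP are taken in both arms on one timetable. The CDSS, for example, "is a nine-item clinician rated outcome measure that assesses the level of depression in people with schizophrenia". Blood pressure, resting pulse, weight and postural stability are also measured in both arms. Section 2.15 covers becoming ill and treatment changes for all participants, the serious-event clause has no arm limit, and section 4 extends reporting beyond the instructors. No safety endpoint is claimed, and a condensed article may leave case-report forms to a fuller protocol.

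Much of this stands. A reader might infer that controls will have no safety data, or that safety cannot be compared at all. The documents do not support that, because symptomatic and physical worsening is measured in both arms. A reader might also infer that an unblinded instructor decides relatedness, or that patients who stop attending are never asked again. Section 5 names no judge of relatedness, and section 2.15 says notes will be made on those who discontinue.

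Two parts do not stand. First, scales at four post-baseline visits do not count events: a relapse or injury between visits may leave no trace in a score, and a patient who is unwell may miss the visit. Second, the condensed format does not explain a stated restriction. Section 5 says whom the instructors ask and which events are recorded, and it conflicts in scope with section 4.

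**Conclusion.** The point holds for adverse event rates. Active enquiry is described in one arm only, and recording under section 5 is confined to events that controls cannot have. Section 4 is broader but still causal, and it adds no enquiry among controls. Relapse, admission and injury therefore cannot be set against their background frequency, even descriptively. The asymmetry is at most 23 session-based enquiries per intervention patient against none per control, affecting the 30 controls.

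Deterioration on the symptom scales and physical measures, and changes of treatment, can still be examined in both arms to a limited extent. The conclusion assumes that the article's wording reflects what will be done and that no all-cause adverse event form is in use at the shared visits. The change is worth making because it is cheap, but it will not turn a trial of 30 per arm into a powered safety comparison.

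**What to change.** - Reconcile sections 4 and 5 so that one statement defines which events are recorded, in whom and by whom.
- At the visits both arms already attend (week 6, week 12, months 6 and 12), ask every participant the same adverse event questions whatever the presumed cause, including psychiatric admission, relapse and injury. Enter the answers in the trial record.
- Report these descriptively by randomised arm, without a claim of powered comparison.
- Keep the instructors' reports as a separate listing for the intervention arm only, so that the extra session-based enquiry does not enter the between-arm counts.

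The cost is one form and a few minutes per existing visit, with no new visits or staff. The remaining limitation is precision: with no events among 30 patients, a true rate of up to 9.5% could not be excluded (one-sided 95%).

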## 6. Results

The pilot study, which was conducted in spring 2023, evaluated the acceptability and feasibility of different perspectives of the intervention, the data collection timeline, and the logistics of the study. This gives the research team valuable lessons to learn and if needed, enable adjustments before entering the main study. Due to the small sample size in the pilot study, we do not evaluate the feasibility in terms of recruitment, measurement completion, attendance rate nor drop-out. We will include the adjustments in the intervention design, data collection and logistics which will be made based on the pilot study and advance to the main RCT study in autumn 2023. We expect to publish the first results of the pilot study in spring 2024.

We expect to publish the first results of the main study in 2026 with the primary, secondary and exploratory results described in detail in section “3. Outcomes.”

## 7. Discussion

Schizophrenia is prevalent in the adult population worldwide. Considering that the pharmaceutical treatment of the illness is far from optimal, cost-effective and easy-access interventions, which can be added on the conventional treatment, are needed. Physical, creative and social activities form an effective strategy, but intervention studies are needed to better understand if and how such activities improve the clinical symptoms, quality of life, physical skills, cognitive and emotional capacities, and facilitate regular participation for this target group.

Our study will investigate several aspects of the ways that mixed exercise program with creative movement may improve symptoms, physical health and quality of life of adults with schizophrenia or schizophrenia-like symptoms. As primary results, we expect to find differences related to the negative symptoms of schizophrenia. As secondary results, we expect to find differences in several variables on general and positive symptoms, physical health, cognitive and emotional capacity and quality of life. To our knowledge, this is the first study to investigate the influence of regular physical exercise with focus on creative, emotional and social activity in people with schizophrenia with a broad spectrum of measures from clinical symptoms to physical health and brain imaging.

Several studies report improved physical and emotional state in people with schizophrenia after regular practice of physical and body-awareness training, respectively (Martin et al., 2016, 2017; Girdler et al., 2019; Millman et al., 2021). However, neuroscientific results for such interventions are still lacking. We aim to connect the clinical and physical outcomes to the outcomes of brain imaging.

The challenge in a holistic intervention combining physical, creative and social components is that we cannot know which individual components contribute to the changed clinical and health outcomes. The influential subcomponents in a positive outcome could be the supportive group setting, instructors, music, or specific parts of movement exercises. However, we hypothesize that the core of the intervention is the *combination* of all these subcomponents together. Methodologically, we follow the highest standards for clinical studies including the randomized controlled design, one-year follow-up and the combination of quantitative and qualitative measures related to clinical symptoms, physical abilities, and cognitive, emotional and cerebral functions.

Several aspects of our trial design are worth noting as potential limitations. Since the sample size is calculated according to the primary outcome PANSS, the results of the secondary outcomes should be considered cautiously, and the results replicated in future studies. If the sample size was calculated according to the amount of all the measurements, the sample size would be so high that it would be beyond realistic possibilities, and this study would very likely never be completed. Some of the measures, such as PANSS, are subjective whereas other measures, such as brain imaging, are objective. Although it is difficult to blind the assessor during the assessment of the objective measures, the person performing the analysis will be blinded. Since this is the first time we use such intervention of creative physical exercise, we cannot know whether the design will be robust enough to capture changes with the content (e.g., physical activity increasing heartrate, social interaction, body awareness) and dosage we defined (twice a week for 60 min per session). However, the content and dosage are based on previous literature on creative movement interventions in schizophrenia (Martin et al., 2016; Cheng et al., 2017; Bryl et al., 2020).

In the pilot study, we tested the feasibility of biweekly attendance, which might be challenging for the participants with schizophrenia. However, in the pilot study, there was a high attendance rate and no dropouts. Nonetheless, we are aware that biweekly commitment implies a behavioral change that can be hard to achieve for this target group. Thus, it is interesting to investigate if the format of this intervention can influence motivation, retention, and interest to participate regularly.

The results from this study will broaden the knowledge of the ways non-pharmacological interventions can be valuable for reducing the burden of schizophrenia for patients themselves, their families, and the healthcare system. Mixed physical exercise with creative movement could be an example of an easy-access joyful intervention as a complementary treatment.

To conclude, this randomized controlled study with 60 participants will investigate the effects of combined physical, creative and social training in adults with schizophrenia. The primary aim is to study the effects of the intervention on negative symptoms of schizophrenia, but several other aspects, such as physical skills and health-status, cognitive and emotional capacity and brain functions related to them as well as movement quantity and mimicry, will also be studied. The results from this intervention study may provide useful information and potentially a complementary treatment to use for caregivers in primary healthcare and psychiatric in- and outpatient clinics.

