### 2.6. Randomization

The participants will be randomly divided into two groups, 30 patients who will receive the mixed exercise program with creative movement intervention in addition to continuing their conventional treatment plan and 30 patients who will only receive their usual treatment. Randomization in the main RCT study will be carried out in sealed envelopes after the baseline measurements. An external statistician will prepare the envelopes that will be delivered to the participants by the research team. Thus, the randomization will be blinded to the research team, meaning the research team will not know the group or identify of the participants when analyzing the data. Due to the nature of intervention studies, blinding toward the participants is not possible. Physical activity cannot be blinded, meaning that the patients know whether they are receiving the treatment or not.

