### 2.11. Procedures

When a patient at the psychiatry clinic is interested in participating in the main study, contact information will be transferred from responsible clinician to doctoral student, who will call the participant, give further information, answer questions if needed, and check inclusion/exclusion criteria. A meeting at the movement laboratory at the hospital will be set up with participant and psychiatrist who will do the PANSS, CGI-S, CDSS, and PSP as well as the doctoral student who will conduct physical tests and measures and test cognitive function combined with functional brain imaging and eye tracking. The baseline measures will take about 2.5 h with a break in between. Data on gender, age, years of education, way of living, years with schizophrenia diagnosis, medication, and smoking will be collected but no other sociodemographic information. The baseline measurements will be conducted 4 to 2 weeks prior to the beginning of the intervention. It may take a few weeks to form a group, and therefore, a 2-week window for the baseline data collection is needed. The participant will be instructed about the accelerometer, which is to be worn for 7 days to evaluate everyday activity. After baseline measures are finished, sealed envelopes will be given to the participants to randomize whether they will be part of the control or intervention group. The participants in the intervention group will be shown videos of the instructors and the training studio, to enable recognition and feeling of safety.

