At session 2, 12, and 23 motion capture will be recorded. Those sessions will take place at the movement laboratory. Participants and one instructor will wear small reflex balls on six points: hands, elbows and knees, while doing the training session. Setting up will be done by an engineer at the movement laboratory or the doctoral student. On week 6 of the intervention the same procedure of tests, apart from the accelerometer, cognitive tests and functional brain imaging, will be repeated. After the last session, about two participants and their family members or other next of kin from each group will be purposefully selected for interview. The get a heterogenic group, we will strive for a variation regarding age, gender, participation rate and severity of disease. The participants and their family member or other next of kin will receive written and oral information about the qualitative study (including assurance of voluntariness and confidentiality), before signing a written consent. After finishing the intervention at week 12 all tests from baseline will be repeated in 1–2 weeks. This will also be done after 6 and 12 months, excluding the accelerometer.

The pilot study was conducted in the same way, except there was no control group or randomization procedure nor cognitive or brain imaging measures, nor will there be any follow-up tests in 6 or 12 months.

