### 3.1. Primary outcome measure

#### 3.1.1. Positive and negative schizophrenia symptom scale (PANSS) negative symptoms subscale

The healthcare professional evaluates the patients with PANSS Negative Symptoms subscale (Cronbach’s alpha of 0.83, Kay et al., 1988; von Knorring and Lindström, 1992) at baseline, at week 6 at and after week 12, PANSS Negative Symptoms subscale will also be collected in the follow-up session; 6 and 12 months after finishing the intervention.

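### Blinding is provided only for the analysis; no masking is described for the psychiatrist who rates the subjective primary outcome after allocation

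*Protocol article*

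**What the plan says.** The protocol article deals with blinding in two places.

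- **Section 2.6 (Randomization).** On the envelopes: "An external statistician will prepare the envelopes that will be delivered to the participants by the research team". It then concludes: "Thus, the randomization will be blinded to the research team, meaning the research team will not know the group or identify of the participants". That sentence goes on to restrict the claim to the time when the data are analysed. The section also states that participants cannot be blinded.
- **Section 7 (Discussion), limitations.** "Some of the measures, such as PANSS, are subjective whereas other measures, such as brain imaging, are objective". The next sentence reads: "Although it is difficult to blind the assessor during the assessment of the objective measures, the person performing the analysis will be blinded".

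The people who produce the primary score are described elsewhere.

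- **Section 3.1.1:** "The healthcare professional evaluates the patients with PANSS Negative Symptoms subscale", at baseline, week 6, after week 12, and 6 and 12 months after the intervention.
- **Section 2.11:** the test visit brings together "participant and psychiatrist who will do the PANSS, CGI-S, CDSS, and PSP as well as the doctoral student". Envelopes are given out once baseline measures are finished.
- **Section 3.2.2 (quality of life, social performance, depressive symptoms):** "The patients’ psychiatrist and a person who knows the patients, such as a family member, will evaluate the state of the patient". This evaluation is made at both ends of the intervention.
- **Table 2:** the PANSS negative subscale is a clinician report, with two items also marked as a report from a family member or other next of kin, at every assessment.

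**The concern.** In an open-label comparison with usual care, masking the outcome rater is the main protection for a clinician-rated scale. A rater who knows the group, and who expects the intervention to help, can score negative symptoms a little lower in that group without intending to. The bias is then in the recorded score. An analyst who does not know which group is which will estimate it faithfully as a treatment effect.

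The article does not simply leave this to a fuller document. It makes statements about blinding, and they are misplaced. Section 2.6 treats concealment of the sequence before assignment as if it gave blinding afterwards. The Discussion takes up assessor masking for the objective measures, where it matters least, directly after naming PANSS as subjective. The single primary comparison is left without stated protection.

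**Working it through.** **Step 1: who is stated to be masked.**

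| Person | Role in the primary outcome | Masking stated |
|---|---|---|
| Participant | Interviewed for PANSS | Not possible (2.6) |
| Psychiatrist or healthcare professional | Scores PANSS (2.11, 3.1.1) | None |
| Next of kin | Reports on two negative items (Table 2) | None |
| Research team | Delivers envelopes (2.6) | When analysing the data only (2.6) |
| Data analyst | Analyses scores | Yes (Section 7) |

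The sections 2.6 and 7 statements agree with each other once the section 2.6 sentence is read to its end: both concern the analysis. Neither reaches the people who generate the score.

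**Step 2: timing.** Allocation is disclosed after baseline (2.6, 2.11). The week 6, week 12, 6-month and 12-month PANSS ratings therefore all follow disclosure. Only the baseline rating is protected by the order of events.

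**Step 3: the inference in section 2.6.** The premise is that an outside statistician prepares sealed envelopes. This supports the conclusion that nobody can foresee the next assignment. It does not support the conclusion that the team stays unaware of an assignment once made. Team members send video-links to participants who miss sessions (2.13) and interview intervention participants just after the last session (3.2.7), so some of them will know.

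**Step 4: what rating bias would do (illustration only).** The documents give no size for it, so the shift *b*, in SD units of the score, is an assumption.

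Inputs:
- 30 per arm and 25% dropout (2.7): 30 × 0.75 = 22.5 evaluable per arm.
- Two-sided 0.05 (3.3.3).
- No true effect.
- A two-sample t-test, as a simple stand-in for the planned analysis.

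The planned N = 60 is not in dispute here and is used only to obtain 22.5.

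Non-centrality is *b* × √(n/2), with √(22.5/2) = 3.354. Degrees of freedom are 2 × 22.5 − 2 = 43, and the critical value is 2.017. The false-positive rate is the probability that the noncentral t falls outside ±2.017.

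| Assumed shift *b* (SD) | Non-centrality | False-positive rate, 22.5 per arm | Same, 30 per arm |
|---|---|---|---|
| 0 | 0 | 5.0% | 5.0% |
| 0.2 | 0.671 | 10.1% | 11.9% |
| 0.3 | 1.006 | 16.6% | 20.8% |
| 0.5 | 1.677 | 37.5% (37.45% before rounding) | 47.8% |

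A normal approximation gives 10.3%, 17.2% and 38.9% at 22.5 per arm, so the choice of formula does not matter. Keeping more patients makes the error worse, because a fixed bias is estimated more precisely.

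**The case against.** The strongest reply is that the article is silent on rater masking, and that silence in a condensed article proves nothing: the full protocol may name a masked rater. That stands to this extent: the documents never say that the PANSS rater is unmasked, and a reader who infers so goes beyond the text. The supportable statement is that no masking of the rater is provided. It does not clear the article, because sections 2.6 and 7 choose to describe blinding and cover only the analysis.

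Three further readings are tempting and should not be pressed.

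- **That the team discloses allocation by delivering envelopes.** The envelopes are sealed and prepared externally, and nothing says that the team opens them or that the rating psychiatrist hands them over. Nor does section 2.6 claim general blinding that delivery would contradict, since the full sentence is confined to the analysis. The fault is the inference from concealment to blinding.
- **That the treating psychiatrist rates PANSS.** Section 3.2.2 refers to the patients' own psychiatrist but does not name PANSS. The link is indirect: the section covers PSP and CDSS, and section 2.11 has one psychiatrist do those scales and PANSS. It is a plausible inference, not a statement.
- **That motion-capture work unmasks the primary outcome.** On motion capture, section 2.11 says: "Setting up will be done by an engineer at the movement laboratory or the doctoral student". The doctoral student does physical, cognitive and imaging tests and does not rate PANSS, so this does not bear on the primary comparison.

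It is also fair that the false-positive figures show what bias would do if present, not that it is present. Finally, Table 2 does not say whether the kin reports enter the score or only inform the clinician, so their influence cannot be judged.

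**Conclusion.** The point holds in this form: the article states blinding only for the analysis, draws a wrong inference from envelope preparation to blinding of the team, and provides no masking for the psychiatrist or next of kin who supply a subjective primary score after allocation in an open comparison with usual care. Followed as written, the plan leaves its single primary comparison open to detection bias that no later analysis can remove.

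The size is unknown. Under the assumptions listed (no true effect, 22.5 per arm, shifts of 0.2 to 0.5 SD chosen for illustration), the chance of a false significant result is about two to seven times the nominal 5%. The conclusion about the text does not depend on those figures. Actual unmasking of the PANSS rater is not documented and is not claimed. The passage should be corrected because it concerns the validity of the primary result and the correction is cheap.

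**What to change.** 1. In sections 2.6 and 3.1.1, state that the psychiatrist who rates PANSS (and CGI, PSP and CDSS) after baseline has no access to allocation and takes no part in sessions or in handing over envelopes. Using psychiatrists already at the clinic, raters should not assess their own patients where this can be arranged.
2. Ask patients and next of kin before each post-baseline rating not to reveal the group to the rater, and record any unmasking.
3. State how the two next-of-kin items enter the PANSS negative score, since kin may know the group.
4. Replace the inference in section 2.6 with a plain list of who is masked and who is not, and keep allocation concealment as a separate statement.
5. In the Discussion, address masking for PANSS as well as for the objective measures, and list any rating of the primary outcome that remains unmasked as a limitation.

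The cost is a small scheduling burden so that patients are rated by someone other than their own psychiatrist where possible, plus a short instruction and a note of unmasking at each visit. No additional assessor needs to be hired.
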